**INTRODUCTION**

Cervical Radiculopathy (CR) is a disorder of the spinal nerve roots that is largely caused by space occupying lesion, disc herniation compression and bony spur typically osteophytes in degenerating cervical spine which can lead to nerve root inflammation, impingement even both [^1^](#_ENREF_1). These lesions can trigger pain receptors in the soft tissues and joints of cervical spine that can lead to both sensory or the motor changes in upper extremity [^2^](#_ENREF_2) along with loss of sensation, numbness, tingling, fragility in upper end point, motor defects in neck and few times in scapula, and pain along the nerves pathway into the hand and arm, relying on where the affected roots are located.

The radiation of pain can be unilateral or bilateral, although bilateral cases occurred only in 5-36% of patients with cervical radiculopathy [^3^](#_ENREF_3)^,^ [^1^](#_ENREF_1). The upper quarter pain involves pain interpreted in the arm, shoulder, upper back, neck and upper chest area which might or not be associating with headache [^4^](#_ENREF_4).

The incidence of cervical radiculopathy annually is about 83.2 per 100 000 people. This incidence increase in the fifth decade of life that reaches to 203 per 100 000 [^3^](#_ENREF_3). It also results from roadside accidents, stenosis, overuse injuries of neck and exercise in bad posture. In 22% of patient’s disc involving diseases are main cause of CR, while combination of both diseases disc related and spondylitic changes include 68% patients. Nerve roots levels which are commonly affected in cervical radiculopathy are C6 and C7 [^5^](#_ENREF_5). Subjects with cervical radiculopathy although complain of neck pain but the main issue for which patient seeks therapy is pain in the arm [^3^](#_ENREF_3).

Among Pakistani population irregular physical activity is common, intensifying stress levels and deficiency of exercise are causing tremendous problems in daily routine. These factors result in bone, immune system and muscles feebleness as well as deteriorate body mechanics. Due to these factors, instability of the spine and related structures aggravate the underlying musculoskeletal problems [^6^](#_ENREF_6).

For establishing criteria for the diagnosis of cervical radiculopathy different diagnostic tests are devised. MRI and EMG are considered the gold standard for diagnosing cervical radiculopathy [^3^](#_ENREF_3). But these techniques are not readily available in most of clinical settings so other manual diagnostic tests are used. For that Wainner et al developed a criterion for diagnosis that is based on four variables. These include 1) Spurling test 2) upper limb tension test ULTT for median nerve 3) distraction test 4) cervical rotation. This clinical prediction rule has specificity of 94% and is useful method for the diagnosis of cervical radiculopathy [^1^](#_ENREF_1).

Cervical radiculopathy can be treated surgically but there is large number of evidence suggesting conservative management to be more effective than surgical treatment, suggesting multimodal treatment strategies that includes cervical traction, manual therapy techniques and strengthening exercises [^7^](#_ENREF_7)^,^ [^2^](#_ENREF_2). Although there is little high-quality evidence on the best non-operative therapy for cervical radiculopathy but these are used to relieve discomfort and pain [^8^](#_ENREF_8)^,^ [^9^](#_ENREF_9).

For this pathology conservative treatment options include therapeutic exercises for gaining strength and improving range of motion, manual therapy techniques along with mobilization and manipulation, use of different modalities such has heating, cryotherapy and traction, soft tissue mobilization techniques, medication and use of cervical collars [^10^](#_ENREF_10). In the present study strengthening exercises will be used as this regimen is successfully used as component of treatment program for patients with cervical radiculopathy [^11^](#_ENREF_11)^,^ [^12^](#_ENREF_12).

Another treatment used for the patients of cervical radiculopathy is neural mobilization technique [^7^](#_ENREF_7). Nervous system can undergo mechanical loads, for that it must be able to adapt and endure mechanical events of sliding, elongation, cross sectional changes, compression and angulation. But when the adaptation mechanism of nervous system fails it can undergo neural edema, fibrosis, hypoxia that can cause alteration in the neurodynamics of nervous system. This concept of neurodynamics by Shacklock is now more accepted term in physiotherapy than neural tension test, that examine the physical ability of the nervous system. This term refers to integrated biomechanical, physiological issues and also includes morphological functioning of the nervous system [^13^](#_ENREF_13)^,^ [^14^](#_ENREF_14). The extent of the neural movement depends on the surrounding tissues. These surrounding structures may impinge the passing nerve due to tightness or nerve may be sliding through the scars of these tissues or the nervous system may be overstretched, swollen and may have abnormal impulse generation[^14^](#_ENREF_14).

Neural mobilization is physical method for treatment of pain. This approach influences physiology of pain through mechanical treatment of neural tissues and the surrounding structures of nervous system. The main aim is to restore the disturbed dynamic balance between the neural tissues and surrounding non neural tissues. This will permit decrease pressure on the neural tissues and enhance optimal physiological functioning [^15^](#_ENREF_15)^,^ [^16^](#_ENREF_16). The benefits achieved through this include nerve gliding, reduced nerve adherence, improved vascularity of neural tissues, noxious fluids are dispersed and axoplasmic flow is improved[^14^](#_ENREF_14)^,^ [^16^](#_ENREF_16).

Neural mobilizations have been studied in various populations such as low back pain, carpal tunnel syndrome, lateral epicondalalgia and cervico-brachial pain [^13^](#_ENREF_13). Neural mobilization techniques studied include cervical lateral glides for cervico-brachial pain in which lateral translatory movement of c-spinal segment to be treated is done with an aim to move the structures surrounding the nerve [^17^](#_ENREF_17), nerve gliding exercises which are sequence of positioning of fingers to elongate median nerve used in the treatment of carpal tunnel syndrome [^18^](#_ENREF_18). However further researches are required for validation of this neural mobilization concept [^13^](#_ENREF_13). In the present study this approach will be used to evaluate its effects on patients with cervical radiculopathy.

Many studies have been done on treatment of cervical radiculopathy. But most of them are inconclusive in terms of defining appropriate treatment options that would be efficacious for the treatment of this pathology. As they lack in quality of study, number of subjects, treatment methods used, duration of sessions, measurements of outcomes, including patients with neck pain of multiple or unspecified origin or conditions masquerading as cervical radiculopathy and comparison of different treatments [^3^](#_ENREF_3)^,^ [^12^](#_ENREF_12) .

The purpose of this study is to assess the neural mobilization technique as an effective treatment for cervical radiculopathy through appropriate randomized controlled trial. Taking the factors and outcome measures under consideration that are not addressed properly in previous literature. As it is a cost effective technique, this study will help many people with cervical radiculopathy. Because of non-availability of different expensive modalities, these manual techniques will enhance the scope of rehabilitation in these subjects.

**OBJECTIVES**

The objective of the study was to compare the effectiveness of neural mobilization technique with conservative treatment on pain intensity, cervical range of motion, disability, cervical muscle endurance and quality of life

**methodology**

**Study design:**

Randomized controlled trial.

**Study setting:**

Physiotherapy department of Mayo Hospital, Lahore.

**Duration of study:**

18 months.

**Sample size:**

88 patients (44 in Group A and 44 in group B) will be included in the study using effect size 0.70, calculated from the parent article using (mean±SD) in group 1 (3.35±1.49) and group 2 (4.45±1.63) ^26^, at level of significance 0.05 and power 90% calculated by using G* Power [^19^](#_ENREF_19).

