**DATA COLLECTION PROCEDURE:**

This randomized trial will be conducted according to consolidated standards of reporting trial CONSORT guidelines (2010) [^20^](#_ENREF_20). This will be parallel group randomized controlled trial with 1:1 allocation ratio into two groups. Study will be conducted at physical therapy department of Mayo Hospital Lahore.

In order to recruit the patients in the study. Patients between ages 35-50 years, willing to participate will be chosen according to inclusion criteria. Patients will be asked to sign a consent form and give their will regarding being enrolled in the study.

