**Constraints:**

Patient regularity and drop out might be a major constraint as my patient population ranges between age of 35-50, individuals in this age have a busy work routine hence once patient feels a little relief, he feels boredom visiting hospital or often leave from work place is an issue, however this issue will be tried to resolve by asking them about their will to complete the study and writing an official letter to their work place if needed and applicable.

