**Data analysis procedure:**

Data will be analyzed on SPSS version 21 and MS Excel 2010. Descriptive analysis (mean, median, mode, variance, standard deviation) will be performed for quantitative data i.e. continuous and discrete variables. Frequencies and percentages will be calculated for categorical and nominal data. For graphical representation, continuous and discrete variables will be presented with histograms with normal curve and categorical and ordinal data will be presented in form of bar and pie charts.

Independent samples t-test and Man Whitney test will be used accordingly for between group comparisons. Repeated measure ANOVA will be used for within group analysis.

Inferential statistics will include independent samples t test and Man Whitney test at various levels of assessment for between group comparison while Freidman and repeated measure ANOVA will be performed for within group analysis separately. Excel 2010 will be used for scatter plotting and routine calculations.

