# Allocation:

# Care Providers

# Allocation :

# Patients

Assessed for eligibility=88

(n = …)

Allocated to intervention (n =44)

Received allocated intervention (n =44)

Did not receive allocated intervention (give reasons) (n = …)

Care providers (n = 1 ), teams (N = 5 ), centers (n= 1 ) performing the intervention

Care providers (n = 1 ), teams (n = 5), centers (n= 1 ) performing the intervention

Allocated to intervention (n =44)

Received allocated intervention (n =44)

Did not receive allocated intervention (give reasons) (n = …)

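### The 88 patients are the bare minimum for 90% power and hold no allowance for loss, so if the dropout that the protocol fears occurs, the planned unadjusted test has less than 90%

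*Protocol*

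**What the plan says.** The Sample size section states: "88 patients (44 in Group A and 44 in group B) will be included in the study using effect size 0.70". The effect size is taken from a published comparison, "mean±SD) in group 1 (3.35±1.49) and group 2 (4.45±1.63", and the calculation is described as "at level of significance 0.05 and power 90% calculated by using G* Power". Whether the test is one- or two-sided is not stated. The trial is a "parallel group randomized controlled trial with 1:1 allocation ratio into two groups".

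The same 88 is the number of envelopes to be prepared (Concealment of allocation) and the number shown as randomised in the flow chart (Research work plan).

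The Constraints section says "Patient regularity and drop out might be a major constraint as my patient population ranges between age of 35-50". It names work routine, waning interest once symptoms ease, and difficulty getting leave. Its response is to ask patients whether they are willing to complete the study and, where needed, to write to the employer. Nowhere does the protocol give an expected loss rate, raise the number for loss, or say that patients who leave will be replaced.

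For the analysis: "Independent samples t-test and Man Whitney test will be used accordingly for between group comparisons". These are unadjusted tests at each assessment. Pain, range of motion, endurance and quality of life are all recorded at baseline (Baseline measurements).

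**The concern.** The power figure and the warning about dropout sit in the same protocol but are not connected. A power of 90% describes the number of patients analysed, whereas 88 is the number randomised. If the two are equal by design, every patient missing at the final assessment comes straight off the number on which the power rests.

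The last assessment follows the twelfth session in week 4. The protocol's own explanation of dropout is that patients stop attending once they feel better, so losses would tend to be greatest at that assessment. An unadjusted t-test or Mann-Whitney test at a given assessment uses only the patients measured then. At stake is how a non-significant result is judged: against the quoted 10% chance of missing the assumed effect, or against a larger one.

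**Working it through.** **Inputs.** From Sample size: means 3.35 and 4.45, SDs 1.49 and 1.63, effect size 0.70, alpha 0.05, power 90%, 44 per arm. Allocation is 1:1 (Data collection procedure). The test is the independent-samples t-test (Data analysis procedure). Loss rates and baseline-outcome correlations are assumptions.

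**Step 1: the effect size.** Pooled SD = √[(1.49² + 1.63²)/2] = √2.4385 = 1.562. d = (4.45 − 3.35)/1.562 = 1.10/1.562 = 0.704. The stated 0.70 is this figure rounded.

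**Step 2: the plan's own number.** The power of a two-sided t-test with n per arm comes from the noncentral t distribution with 2n − 2 degrees of freedom and noncentrality d√(n/2). With d = 0.70:

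- n = 44: noncentrality 0.70 × √22 = 3.283, power 90.1%
- 44 and 43: 89.75%
- n = 43: 89.4%

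The smallest n reaching 90% is 44, so the total of 88 is reproduced exactly. A one-sided test would need 36 per arm (72 in total). That does not give 88, and with a 20% allowance it would give 72/0.80 = 90. The stated number therefore matches a two-sided test with no allowance for loss.

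**Step 3: power if 88 are randomised and some are lost.** Analysable n per arm = 44 × (1 − loss), with loss equal in both arms and d = 0.70. The last column is the total to randomise to keep 44 analysable per arm: 2 × 44/(1 − loss), rounded up per arm.

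| Assumed loss | Analysable per arm | Power, unadjusted t-test | Total to randomise to keep 44 per arm |
|---|---|---|---|
| 0% | 44.0 | 90.1% | 88 |
| 5% | 41.8 | 88.5% | 94 |
| 10% | 39.6 | 86.8% | 98 |
| 15% | 37.4 | 84.8% | 104 |
| 20% | 35.2 | 82.5% | 110 |
| 25% | 33.0 | 80.0% | 118 |
| 30% | 30.8 | 77.1% | 126 |

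The type II error rises from about 10% to 13.2% at 10% loss, 17.5% at 20% and 20.0% at 25%.

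**Step 4: what baseline adjustment would return.** ANCOVA on the baseline value reduces the residual SD by the factor √(1 − r²), where r is the within-arm baseline-outcome correlation. The effective standardised difference becomes 0.70/√(1 − r²), with one degree of freedom fewer. At 20% loss (35.2 per arm):

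| r | Effective d | Power |
|---|---|---|
| 0 | 0.700 | 82.5% |
| 0.2 | 0.714 | 84.0% |
| 0.3 | 0.734 | 85.9% |
| 0.4 | 0.764 | 88.5% |
| 0.5 | 0.808 | 91.7% |

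The same formula passes 90% at about r = 0.45.

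**The case against.** **The warning is tentative and is answered.** The protocol says only that dropout might be a constraint, gives no rate, and lists countermeasures. This stands. A reader might infer that the trial will not have 90% power; the documents do not support that. They support only that power falls below 90% if the feared dropout occurs.

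**The arithmetic is right.** This also stands. The gap is a missing allowance for loss, not a miscalculation.

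**The margin turns on rounding.** With the unrounded d = 0.7044, 44 per arm gives 90.4%, one loss leaves 90.1%, and one loss per arm gives 89.8%. So the statement that no patient can be spared is exact only at the stated 0.70. One or two losses are trivial either way; the table above is the relevant scale.

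**The effect size matters more.** With no loss at all, d = 0.60 would give 79.5%. That is true, but it is a separate uncertainty and does not remove this one.

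**The flow chart.** It carries "Assessed for eligibility=88" beside 88 randomised, and a reader might infer that each screening failure also reduces power. It does not: patients are pretested first, and an envelope goes only to those found eligible (Concealment of allocation). The chart also leaves exclusions, losses and numbers analysed blank. The entry is at most an editorial slip in a template.

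**Unseen material.** The formula figure is not shown and a separate SAP may exist. Since 88 is reproduced without any loss term, a hidden allowance is unlikely. An SAP might plan a more efficient analysis, but the power claim itself is fixed in the protocol.

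**Conclusion.** The point holds in conditional form. The 88 patients are the exact minimum of analysable patients for 90% power at d = 0.70 and two-sided alpha 0.05. The protocol adds nothing for loss, although it names dropout as a possible major constraint.

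If loss occurs, the unadjusted t-test loses about 3 percentage points of power at 10% loss, 8 at 20% and 10 at 25%; it drops below 80% only beyond about 25%. This rests on assumed loss rates, equal loss in both arms, the t-test rather than the Mann-Whitney test, and a true effect of 0.70.

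A reader might also infer that baseline adjustment makes the whole problem disappear. The protocol gives no baseline-outcome correlation, so that cannot be claimed: at 20% loss, adjustment closes less than half the gap at r = 0.2 or 0.3, and closes it fully only from about r = 0.45.

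**What to change.** 1. In Sample size, say which number the power belongs to, for example: *44 analysable patients per arm give 90% power (two-sided alpha 0.05, d = 0.70); with 10-20% loss the unadjusted t-test has about 83-87%.* Add the loss rate the team expects and its basis.
2. In Data analysis procedure, replace the unadjusted between-group test with a baseline-adjusted comparison (ANCOVA on the baseline value already collected). State that the gain depends on the correlation: at 20% loss, about 84% power at r = 0.2, 86% at r = 0.3, 88% at r = 0.4 and 92% at r = 0.5.
3. As a separate editorial correction, leave the number assessed for eligibility open in the flow chart.

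The cost is a sentence or two, a change of analysis using data already planned, and a slightly less favourable stated power. No extra patients are needed. If the team would rather keep 90% for the unadjusted test, the alternative is to randomise more, 98 in total at 10% loss or 110 at 20%, with envelopes to match.

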**Formula**:

[figure not shown]

**Sampling technique:**

Convenience sampling.

**Sampling criteria:**

**Inclusion criteria:**

- Age group between 35-50 years
- Gender both male and female
- Subjects having radiating symptoms of cervical radiculopathy
- Subjects with no previous cervical surgeries
- Subjects with no loss of the upper limb movement

**Exclusion criteria:**

- Subjects having traumatic history
- Subjects with Osteoporosis
- Hypermobile patients
- Subjects with circulatory disturbances
- Subjects with peripheral nerve entrapment
- Subjects with tumor causing cervical radiculopathy
- Patients who are not willing to be included in the study.

# **ETHICAL CONSIDERATIONS**

1. It will be gained prior from the Ethical Committee of the University before study
2. Written informed consent will be taken from all the patients
3. All information and collected data will be kept confidential.
4. Participants will remain anonymous throughout the study.
5. The subjects will be informed that there are no disadvantages or risks on the procedure of the study.
6. They will also be informed that they will be free to withdraw at any time during the process of the study.

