**Group B (control group):**

In group B conservative treatment will be given which will include cervical isometrics exercises with 10 repetitions in each direction with 5 seconds hold will also be given. Isometric exercises will be performed with the patient in sitting position 3 sets of these exercises will be performed with the rest period of 30seconds.

All the subjects will be given hot packs for 10 minutes prior to the treatment.

Subjects having the same baseline will be given treatment for 12 sessions (3 times per week for 4 weeks). Pre assessment will be done at baseline, second assessment will be done after 2 weeks and final post assessment will be done at the end of 12^th^ session in 4^th^ week.

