# **Outcome measures:**

# The main outcome will be the effectiveness of neural mobilization technique on pain intensity measured on VAS, endurance measured by cranio cervical flexion test and range of motion measured on inclinometer. Secondary outcomes will be to see the effectiveness of conservative treatment and measuring the effects of treatment on quality of life [^24^](#_ENREF_24).

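### The protocol commits the trial to telling every patient that there are no disadvantages or risks, which conflicts with its own account of the visit and work burden, and the visible text plans no adverse-event recording.

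*Protocol*

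**What the plan says.** - **Consent message.** Protocol, Ethical Considerations, item 5: "The subjects will be informed that there are no disadvantages or risks on the procedure of the study". It carries no qualifier such as known, serious or expected. Item 2 of the same list requires written informed consent from all patients.
- **Visit load.** The section on Group B, in text that covers both groups, sets 12 sessions, three a week for four weeks. Assessments are at baseline, at two weeks and at the end of the twelfth session.
- **Burden.** Under Constraints, attendance and drop-out are named as a possible major problem because these patients have busy working lives. Once a patient feels some relief, "he feels boredom visiting hospital or often leave from work place is an issue". An official letter to the employer is offered where needed.
- **State of the evidence.** The Introduction says that the neural mobilization concept needs more research before it is validated, and that there is little high-quality evidence on the best non-operative therapy.
- **Outcomes.** The main outcomes are pain on the VAS, cranio-cervical flexion endurance and range of motion. For the rest, "Secondary outcomes will be to see the effectiveness of conservative treatment and measuring the effects of treatment on quality of life". The Neck Disability Index is also collected. No adverse-event or harms item appears in the outcome sections, the baseline list, the data analysis section or the visible part of the questionnaire.
- **Flow diagram.** The Research Work Plan has blank fields for loss to follow-up and for discontinued intervention, each asking for reasons.
- **Exclusions.** These include "Subjects with Osteoporosis", "Hypermobile patients" and "Subjects with circulatory disturbances". No reason is given for any of them.

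**The concern.** Item 5 is an instruction about what patients are told before they consent. If it is wrong on the protocol's own text, every consent in the trial rests on an incorrect statement. Part of it (*disadvantages*) is contradicted elsewhere in the protocol, and the other part (*risks*) is asserted without support.

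The trial as described also has no planned way to learn whether the assurance was justified patient by patient. The outcome scales give group averages at fixed assessments. An event between assessments in a patient who continues treatment, such as a flare of arm symptoms after a session, has no place to be written down. What is at stake is the validity of consent and the trial's ability to report harms by arm.

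**Working it through.** The point is mainly textual, and the plan states no figure that could be reproduced. The relevant places are set side by side first. Some arithmetic on size follows.

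**1. *No disadvantages* against Constraints and the schedule.** Item 5 denies any disadvantage. The schedule requires 12 attendances in 4 weeks, and Constraints describes taking leave from work as a problem for this age group, serious enough to plan a letter to employers. Both statements cannot stand. This step needs no outside source and no inference.

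**2. *No risks* against the evidence described.** The protocol documents no hazard of either treatment, so it does not show the claim to be false. It offers nothing to support it either: the Introduction presents the technique as still needing validation. The fault is an unqualified assurance without a basis.

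**3. What is captured about worsening.**

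| Kind of information | Planned in visible text? |
| --- | --- |
| Average change in pain, disability and quality of life, in either direction, among assessed patients | Yes: VAS, NDI and SF-36, with comparisons between groups at the assessments |
| Reason for loss or discontinuation | Yes: fields in the flow diagram |
| Individual adverse events in patients who stay | No |

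**4. Size.** Inputs are from Sample size (88 patients, 44 per group) and the schedule (12 sessions).

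- Patients who receive the statement: all 88.
- Planned treatment contacts with full attendance: 88 × 12 = 1,056. This is a maximum, since Constraints itself expects irregular attendance.
- Upper limit if events were recorded and none were seen, one-sided 95%: 1 − 0.05^(1/n). For n = 44: 1 − 0.05^(1/44) = 0.066, or 6.6%. For n = 88: 1 − 0.05^(1/88) = 0.033, or 3.3%. So even a clean record could not establish the absence of risk.
- Chance of at least one event among 44 patients in an arm: 1 − (1 − p)^44. The protocol gives no event rate, so p is an assumption, shown over a range:

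| Assumed rate p | 1 − (1 − p)^44 |
| --- | --- |
| 1% | 1 − 0.99^44 = 0.36 |
| 2% | 1 − 0.98^44 = 0.59 |
| 5% | 1 − 0.95^44 = 0.895 |
| 10% | 1 − 0.90^44 = 0.99 |

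Recording would very probably pick up events that affect 5% or more of an arm, and could well miss rarer ones. These figures concern seeing an event at all. They say nothing about power to compare arms.

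**The case against.** The strongest reply has five parts.

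- **Worsening is measured.** A reader might infer that the trial could not detect one arm doing worse, or could report benefit only. The protocol does not support that. The VAS is taken before, during and after treatment, the NDI and SF-36 can move in either direction, and groups are compared at the assessments. This part of the reply stands. What remains is the narrower gap: individual events in patients who continue.
- **Drop-out reasons are collected.** A reader might also infer that withdrawal because of worsening would disappear into ordinary loss and bias the main comparison. The flow diagram has separate entries with reasons for loss and for discontinuation, so that inference fails, and no effect on the main comparison is shown.
- **The exclusions prove nothing.** It is tempting to read osteoporosis, hypermobility and circulatory disturbance as admitted risk groups. The protocol gives no reason for any exclusion, so a safety motive is only an inference. Even if it is right, excluding such patients lowers risk for those enrolled and does not contradict what the enrolled are told. The point does not rely on it.
- **Item 5 may mean only the procedures, not attendance.** The wording allows that reading, and patients are to be asked about their willingness to complete the study. But attending for treatment is part of taking part, and the word *disadvantages* is not limited. The tension is modest but real.
- **Not all forms can be seen.** The consent pages are not in the text at hand and the questionnaire breaks off within the NDI. A later form item or better consent wording may exist, so the absence of recording is claimed only for the visible text. Item 5 itself is a stated commitment and stands regardless.

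**Conclusion.** The point holds in a limited form. Item 5 is wrong as written: its denial of disadvantages conflicts with the protocol's own schedule and Constraints section, and its denial of risks has no support in the document. It affects all 88 consents. In the visible text, no dedicated adverse-event record is planned across up to 1,056 treatment contacts, so individual events in patients who stay would not be captured.

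The conclusion does not claim that either treatment is hazardous, and it does not touch the primary results. It rests on item 5 being used as written and on the unseen form pages holding no adverse-event item. If such an item exists, the recording part falls away and the consent wording remains. The correction should be made, because it concerns valid consent and patient safety and costs little.

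**What to change.** 1. Reconcile item 5 of Ethical Considerations with the treatment schedule and Constraints. Replace it with a statement of the foreseeable burdens and discomforts of taking part, including the visits and time away from work. The content on discomforts is for the investigators and the ethics committee to judge.
2. Add one line per visit to the case report form for adverse events, including increased arm or neck symptoms.
3. Tabulate adverse events by arm, together with the reasons for loss and discontinuation that the flow diagram already asks for.

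The cost is revised consent wording, notification of the ethics committee, one form line per visit and one table. Treatment, sample size and the efficacy analysis are unchanged.
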